**Table 2. Overall response of target lesions**

|           |                                                                                                                                                                                                                                                                                         |
|-----------|-----------------------------------------------------------------------------------------------------------------------------------------------------------------------------------------------------------------------------------------------------------------------------------------|
| CR | All TLs disappear since baseline. The short axis of any pathological lymph nodes selected as TLs must be less than 10 mm.                                                                                                                                                               |
| PR | The sum of diameters of TLs decreases by at least 30% from baseline.                                                                                                                                                                                                                    |
| SD | Neither sufficient shrinkage to qualify for PR nor sufficient increase to qualify for PD.                                                                                                                                                                                               |
| PD | The sum of diameters of TLs increases by at least 20% compared with the minimum diameter in the trial (including the baseline sum, if this is the minimum value in the trial). In addition to a relative increase of 20%, the sum must also show an absolute increase of at least 5 mm. |
| NE | Only relevant TLs are not assessed or not evaluable or have lesion intervention.

Note: If the sum of diameters meets the criteria of PD, the lesion is not evaluable and should be classified as a PD.                                                                           |

### **9.1.5 Duration of Response (DoR)**

DoR is defined as the time from the date of first compliance with response to the date of PD or death due to any cause. The end date of the response should be

consistent with the date of the endpoint PFS. The start of DoR is defined as the latest date of the visit at which PR or CR criteria are first met. If a subject does not progress after a response, the censored time for PFS will be used for DoR.

## **9.2 Safety Evaluation**

All safety data will be summarized at the end of the study. All data from the initiation of treatment until 30 days after the last dose will be summarized together in the safety evaluation. Data prior to initiation of treatment will be summarized but not included in the summary table of AEs.

## **9.3 Recommended Toxicity Management**

During toxicity management, the dose reduction for adverse events of apatinib will be permitted to 250 mg every other day. If a subject still cannot tolerate the treatment despite receiving the lowest dose, it is recommended to discontinue the study treatment.

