| Sponsor: Chinese PLA General Hospital
(301 Military Hospital)                                                                                                                                                                                                                                                                                                                                                                                                                                                                                                                                                                                                                                                                                                                                                                                                                                                                                                                                                                                                                                                                                                                                                                                                                                                                                                                                                                                                                                                                                                                                                                                                                                                                                                                                                                                                                                                                                                                                                                                                                                                                                                                                                                                                                                                                       | Study Drug: aumolertinib, apatinib                          |

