## 4. Research Background and Scientific Basis

### 4.1 Background

Lung cancer is one of the most common malignancies in the world. In 2018, cancer data from China indicated that lung cancer had the highest incidence and mortality rates, accounting for more than 20%. Non-small cell lung cancer (NSCLC) accounts for 80%-85% of all lung cancers, approximately 70% of lung cancer patients are already at an advanced stage, either locally or with distant metastasis, by the time of initial diagnosis, making surgical resection unfeasible. Additionally, patients who initially undergo successful surgical resection later develop distant metastases by the time of relapse. The median survival of patients with advanced NSCLC who cannot be surgically resected is often less than one year.

Epidermal growth factor receptor (*EGFR*) sensitive mutations (*EGFRm+*) are the most common driver gene mutations in NSCLC, accounting for 10%-17% of Western populations and 30%-50% of Asian populations. Tyrosine kinase inhibitors (TKI) targeting *EGFR*-sensitive mutations have become the first-line standard treatment for locally advanced or metastatic NSCLC with *EGFRm+*, with progression-free survival (PFS) of 8-18.9 months. But patients who initially respond to EGFR-TKIs will inevitably develop disease progression due to secondary resistance. Therefore, it is urgent to delay or overcome EGFR-TKIs resistance, improve patients' PFS and overall survival (OS), and explore new treatment options.

Vascular endothelial growth factor receptor (VEGFR) is a signaling pathway parallel to *EGFR* but intersecting downstream. VEGFR tyrosine kinase inhibitors inhibit the VEGFR signaling pathway, control tumor angiogenesis, and may play a role in EGFR-TKI resistance. The combination of anti-angiogenic agents and EGFR-TKI, inhibiting both VEGFR and EGFR pathways, improves the response to

targeted therapy and delays the onset of acquired resistance in NSCLC patients.

Currently, the combination therapy of anti-angiogenic drugs and EGFR-TKI (also known as "A+T" combination therapy) has been shown to be effective in NSCLC. Domestic and foreign guidelines such as ESMO and CSCO have recommended "A+T" as the first-line treatment for *EGFR* driver gene positive in advanced NSCLC patients .

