## 7. Study Design and Description

### 7.1 Study Design

This is a multi-center, randomized, open-label, phase II clinical trial to evaluate the efficacy and safety of aumolertinib plus apatinib vs. aumolertinib monotherapy as first-line treatment in subjects with epidermal growth factor receptor mutation-positive (*EGFR*m+) advanced NSCLC. Subjects who meet the eligibility criteria will be randomized to the aumolertinib + apatinib group (test group) or the aumolertinib monotherapy group (control group) in a 1:1 ratio. Subjects in the test group will receive oral administration of aumolertinib 110 mg and apatinib 250 mg once daily, and subjects in the control group will receive oral administration of aumolertinib 110 mg once daily, in order to compare the efficacy and safety of the two treatment regimens. The schematic overview of the study is shown in Figure 1.

[figure not shown]

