### **8.3 Follow-up Period**

Subjects who discontinue the treatment due to meeting the discontinuation criteria should complete the treatment discontinuation follow-up, the 30 days safety follow-up after treatment discontinuation, and survival follow-up once every 12 weeks ( $\pm 7$  days) as specified in the study plan.

Subjects without progressive disease at treatment discontinuation will be followed up once every 6 weeks ( $\pm 7$  days) until progressive disease assessed by investigator per RECIST 1.1 (both intracranial and systemic), even if the subject has received other anti-tumor treatments; after progressive disease, the subjects will be followed up for survival once every 12 weeks as specified in the study plan.

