#### **9.1.2 18-month Progression-free Survival (PFS) Rate**

PFS is defined as the time from randomization to the first time of disease progression (assessed by RECIST v1.1) or death, whichever occurred earlier, evaluated by investigators. Patients with treatment discontinuation for any reason will be censored at the date of the last progression assessment with no documented progression. PFS-derived data are based on assessment date rather than visit date.

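### PFS is censored at any treatment discontinuation although scans continue to progression, and section 9.3 adds an ambiguously worded stopping trigger that only the test arm has

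*Protocol*

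**What the plan says.** Four parts of the protocol bear on this.

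- **Censoring (9.1.2).** After defining PFS from randomization to investigator-assessed progression or death, the section states: "Patients with treatment discontinuation for any reason will be censored at the date of the last progression assessment with no documented progression". The rule covers both arms. Under 9.1.5, a responder who has not progressed takes the PFS censoring time for duration of response.
- **Follow-up (8.3).** "Subjects without progressive disease at treatment discontinuation will be followed up once every 6 weeks", until RECIST 1.1 progression, "even if the subject has received other anti-tumor treatments".
- **Toxicity management (9.3).** One reduction step is given: "the dose reduction for adverse events of apatinib will be permitted to 250 mg every other day". Then: "If a subject still cannot tolerate the treatment despite receiving the lowest dose, it is recommended to discontinue the study treatment". No section says that apatinib may be stopped while aumolertinib continues.
- **What the treatments are.** The synopsis gives the study drug as "aumolertinib, apatinib". Section 7.1 says "subjects in the control group will receive oral administration of aumolertinib 110 mg once daily". Section 4.1 says that TKIs directed at EGFR-sensitizing mutations "have become the first-line standard treatment for locally advanced or metastatic NSCLC" with such mutations.

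The primary test (10.1.1) compares the two arms' Kaplan-Meier estimates at 18 months, so the censoring rule feeds directly into it.

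**The concern.** A patient who stops treatment without progression leaves the risk set at the last clean scan. On the plain reading of 9.1.2, a progression found at a later 8.3 scan is not an event, although the trial paid for the scan and holds the result. Kaplan-Meier then treats the patient as if the later risk were that of patients still on treatment. If stopping a drug raises the risk of progression, the censoring is informative and the 18-month rate is overstated.

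The rule applies to both arms, but one route to it does not: apatinib intolerance can arise only in the test arm. Section 9.3 governs that route, and its wording leaves two questions open.

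- **For the patient:** does intolerance of apatinib also end aumolertinib, which a control patient would keep?
- **For the analysis:** if only apatinib stops, is that a treatment discontinuation under 9.1.2? With about 20 sites planned, different investigators may answer differently, and the primary endpoint would be handled inconsistently.

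**Working it through.** **Textual check.** The possible meanings of 9.3 against the censoring rule in 9.1.2:

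| Meaning of 9.3 | Aumolertinib | PFS under 9.1.2 |
|---|---|---|
| Both drugs stop | withdrawn | censored; later 8.3 progressions not counted |
| Only apatinib stops | continues | not stated |

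Neither row gives a satisfactory result. The withdrawal and discontinuation criteria mentioned in 8.2 are not listed, and Appendix A shows the two drugs in separate rows without a stopping rule. Neither settles the matter.

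**Protocol inputs.** Section 6 gives 18-month PFS rates of 75% (test) and 50% (control), with 49 per arm. The total of 98 reproduces with a one-sided 0.05 test and unpooled variance: (0.1875 + 0.25) × (1.645 + 0.842)² / 0.25² = 43.3, so 44 per arm, and 44/0.9 = 48.9, so 49. This does not bear on the present point. The protocol gives no rate of stopping for apatinib toxicity, so everything below is illustrative.

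**Assumptions (not protocol figures).** PFS is exponential. A share f of the test arm, 10% or 20%, stops at month t = 3 or 6 if still event-free. All others keep the planned 75%. After the stop the hazard is h.

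**Hazards.**
- Test: hT = −ln(0.75)/18 = 0.01598 per month.
- Control: hC = −ln(0.50)/18 = 0.03851 per month.
- Midway: (hT + hC)/2 = 0.02725 per month.

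**Formulas.**
- Rate with all progressions counted: A = (1 − f) × 0.75 + f × exp(−hT × t) × exp(−h × (18 − t)).
- Rate targeted by Kaplan-Meier when stoppers are censored at t: B = 0.75.
- Overstatement: B − A.

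**Worked case.** For f = 0.20, t = 3, h = hC: exp(−0.0479 − 0.5776) = 0.535, so A = 0.600 + 0.107 = 0.707 and B − A = 4.30 points.

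**Overstatement of the test-arm rate, in percentage points:**

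| Hazard after the stop | f=10%, t=3 | f=10%, t=6 | f=20%, t=3 | f=20%, t=6 |
|---|---|---|---|---|
| unchanged (hT) | 0 | 0 | 0 | 0 |
| midway | 1.17 | 0.95 | 2.33 | 1.90 |
| control (hC) | 2.15 | 1.78 | 4.30 | 3.55 |
| twice control (2 × hC) | 4.50 | 3.89 | 9.00 | 7.79 |

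The control row fits a patient who carries on with aumolertinib alone. The last row is one guess at what follows if both drugs stop.

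**Different stop timing.** If the stops are spread over the 18 months instead, with 10% or 20% stopping net of progression, the true rate is 73.6% or 72.2% at the control hazard. That is an overstatement of 1.4 or 2.8 points. At twice control it is 72.0% or 68.9%, or 3.0 or 6.1 points. The size therefore depends on timing as well as on the hazard.

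**Scale.** Ignoring censoring, the SE of the difference at 49 per arm is sqrt(0.75 × 0.25/49 + 0.50 × 0.50/49) = 9.4 points. The planned difference is 25 points. The largest value in the control row, 4.30, is just under half an SE.

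**Offset from the control arm.** Control patients censored on stopping add no shift if their hazard stays at hC. If 10% of them stop at month 6 and their hazard doubles, the control rate is also overstated: 0.10 × (0.50 − exp(−0.2310 − 0.9242)) = 0.10 × (0.50 − 0.315) = 1.85 points.

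**The case against.** **Section 9.3 may mean apatinib only.** The sentence before the disputed one concerns apatinib alone, and the protocol defines a reduced dose for no other drug. Study treatment is nowhere defined; the synopsis field names the products and is not a stopping unit. The section is also advisory in its title and its verb, and 8.2 leaves much to the investigator's judgement. All of this stands. A reader might infer that the protocol orders standard therapy to be withdrawn from patients who cannot tolerate apatinib. The text does not support that: it makes a recommendation that can be read this way, and no section forbids continuing aumolertinib. The milder reading does not close the gap, however, because it leaves the censoring status of an apatinib-only stop undefined.

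**The censoring problem belongs to 9.1.2, not 9.3.** This is correct. Any-reason censoring would exist in both arms however 9.3 were worded. What 9.3 contributes is one additional trigger, of unknown frequency, in one arm.

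**Section 9.1.2 could be stretched.** Its last progression assessment might be taken to include scans after discontinuation. But then discontinuation would not affect the censoring date at all, and the sentence would have no purpose.

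**Conclusion.** The point holds as a minor one. As written, 9.1.2 sets aside progressions that 8.3 collects, and this enters the primary comparison. Section 9.3 adds a trigger found only in the test arm and leaves unclear which drugs stop and whether PFS is then censored.

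The size cannot be derived from the protocol. Under the assumed 10-20% of stops at month 3 or 6, the test-arm rate is overstated by 0 points if the hazard does not change and by about 2-4 points if it rises to the control hazard. It would be more if both drugs stop and the hazard exceeds control. Part of it would cancel between arms if control stoppers are informatively censored too.

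A reader might take the 2-4 points as the size of the 9.3 defect, or as the bias in the treatment difference. They are neither. The control hazard describes patients who remain on aumolertinib, not those who lose both drugs. Only the test arm is shifted in that figure, and the stop rates, times and hazards are all assumed. The figures illustrate what the 9.1.2 rule can do and do not bound the net effect.

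**What to change.** In 9.1.2, replace the any-reason censoring sentence with:

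> Progression or death is counted regardless of discontinuation of one or both drugs; patients without an event are censored at the last progression assessment.

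In 9.3, replace the last sentence with:

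> If toxicity persists on apatinib 250 mg every other day, apatinib is stopped permanently and aumolertinib 110 mg once daily may continue; aumolertinib is stopped if the toxicity is attributed to it or persists after apatinib is stopped.

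This wording avoids stopping both drugs by default when attribution is unclear, because apatinib is withdrawn first.

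The cost is a few sentences in an amendment. Assessments every 6 weeks are already scheduled on treatment (8.2) and after discontinuation (8.3), so no patients, visits or scans are added. Investigators would need to record which drug was stopped and, where aumolertinib is stopped, why. The downside is that the test-arm 18-month rate may come out slightly less favourable.

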## **10. Statistical Analytical Methods**

To assess the between-group differences, we will use (i) the Chi-square test for categorical variables, (ii) the Mann-Whitney test for continuous variables, (iii) the Kaplan-Meier method and the Log-rank test for time-to-event variables, and (iv) the “naïve” test based on the comparison of Kaplan-Meier estimators for the 18-month PFS rate (“Fixpoint.test” function of the R package: ComparisonSurv). Hazard ratios (HRs) and corresponding 95% confidence intervals (CIs) will be estimated using the Cox proportional hazards model. The 95% CIs for ORR will be generated through the Clopper-Pearson method. Univariable and multivariable analyses of PFS and ORR will be performed with the Cox proportional hazards model and the logistic regression model, respectively. The interaction effect between treatment and each key variable will be calculated using a Cox proportional hazards model (for PFS) or a logistic regression model (for ORR) that contains the treatment group, key variable, and treatment-by-variable interaction term. All statistical analyses mentioned above will

be performed using IBM SPSS Statistics 22 or R 4.1.3.

## **10.1 Efficacy Analysis**

Efficacy endpoints will be analyzed in Full analysis set (FAS) using results evaluated by the investigator as per RECIST 1.1.

### **10.1.1 Analysis of Primary Efficacy Endpoint (18-month PFS rate)**

The difference in 18-month PFS rate between the two arms will be assessed with the “naïve” test based on the comparison of Kaplan-Meier estimators (“Fixpoint.test” function of the R package: ComparisonSurv).

### **10.1.2 Analysis of Secondary Efficacy Endpoints**

#### **a) Analysis of Systemic PFS**

The difference in PFS between the two arms will be evaluated with the Log-rank test. The HR and its 95% CI will be calculated using the Cox proportional hazards model.

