#### **Calculation of Sample Size:**

Given assumptions of 18-month PFS rate of 75% for aumolertinib plus apatinib and 50% for aumolertinib alone, a drop-out rate of 10%, at the significance level of 0.05, to achieve the power of 0.8, a total number of 98 subjects are needed (49 per arm).

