#### **7.4 Randomization**

This is a randomized, controlled, open-label, multicenter clinical trial. In this trial, randomization will be done by stratified blocked randomization (block size: 4)

using Clinflash IRT (Clinflash Healthcare Technology (Jiaxing) Co. Ltd., Zhejiang, People's Republic of China). The subjects will be randomized in a 1:1 ratio to the aumolertinib + apatinib group or the aumolertinib monotherapy group with *EGFR* mutation status (exon 19 deletion *vs.* exon 21 L858R *vs.* atypical mutations) and metastatic site (CNS metastasis *vs.* no CNS metastasis) at enrollment as stratification factors.

Eligible subjects will be assigned a unique randomization number on the day of the first dose of the investigational medicinal product (the first day of the first treatment cycle, C1D1). The investigator will assign a randomization number and medication number to all screened eligible subjects who qualify for the study after randomization.

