#### **b) Analysis of ORR**

The difference in ORR between the two arms will be assessed with the Chi-square test. The 95% CIs for ORR will be generated through the Clopper-Pearson method.

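### The named efficacy tests ignore the two factors that stratify the randomisation; for PFS this costs power and pulls the hazard ratio toward 1 only if those factors are strongly prognostic

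*Protocol*

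**What the plan says.** Protocol Section 7.4 describes stratified blocks of four, allocated 1:1. EGFR mutation status (exon 19 deletion, L858R, atypical) and CNS metastasis (yes, no) are recorded "at enrollment as stratification factors".

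The comparisons between arms are then named endpoint by endpoint:

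- Primary, Section 10.1.1: "The difference in 18-month PFS rate between the two arms will be assessed with the" fixed-point test of two Kaplan-Meier estimates, with the R function given by name.
- PFS, Section 10.1.2 a): "The difference in PFS between the two arms will be evaluated with the Log-rank test", with a Cox model for the hazard ratio.
- ORR, Section 10.1.2 b): "The difference in ORR between the two arms will be assessed with the Chi-square test".
- DoR, Section 10.1.2 c): log-rank and Cox.
- OS has no entry of its own in Section 10.1.2. It falls under the general line in Section 10, which assigns Kaplan-Meier and log-rank to time-to-event variables.

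None of these mentions strata. Section 10 also plans multivariable Cox (PFS) and logistic (ORR) models and interaction models, without naming covariates. Section 10.1.3 plans PFS comparisons within CNS-metastasis and mutation subgroups.

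**The concern.** Stratified blocks force the arms to be nearly balanced on the two factors. If the factors predict PFS, that balance makes the treatment comparison more precise than an unstratified test assumes. The test then rejects less often than its nominal level under the null and loses power under the alternative. For the Cox model there is a second effect: leaving out a strong prognostic factor moves the hazard ratio toward 1 compared with the ratio within strata.

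A trial of 98 patients has little precision to spare, and the stratum of every patient is known from randomisation. How much is at stake depends on how prognostic the factors are, and the protocol gives no figure for that.

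**Working it through.** **The plan's own figure.** Inputs from the synopsis and Section 6: 18-month PFS 75% and 50%, 10% drop-out, and the condition "at the significance level of 0.05, to achieve the power of 0.8".

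n per arm = [p₁(1−p₁) + p₂(1−p₂)] × (z_α + z_β)² / (p₁−p₂)² = (0.1875 + 0.25) × (1.645 + 0.842)² / 0.25² = 0.4375 × 6.185 / 0.0625 = 43.3, rounded up to 44. Then 44 / 0.9 = 48.9, so 49 per arm and 98 in total.

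The figure reproduces, with a one-sided 0.05 that the text does not state. That is a separate matter. The formula contains no strata.

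**Number and size of strata.** 3 × 2 = 6 strata, on average 98 / 6 = 16.3 patients each. The protocol gives no stratum sizes. Assuming 50/42/8% for exon 19 deletion / L858R / uncommon and 30% CNS metastasis, the smallest of six cells holds 98 × 0.08 × 0.30 = 2.4 patients over both arms. Collapsing to exon 19 deletion versus other, by CNS metastasis, makes the smallest of four cells 98 × 0.50 × 0.30 = 14.7.

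**Log-rank power with four strata.** Simulated: 98 patients, stratified blocks of 4, true hazard ratio 0.50, two-sided 0.05, control 18-month PFS 50%, 10% drop-out, the prevalences above, 3,000 trials per row. Factor hazard ratios are for L858R / uncommon / CNS metastasis and are assumptions.

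| Factor effects | Unstratified | Four strata | Change (points) | Null rejection, unstratified | Null rejection, four strata |
|---|---|---|---|---|---|
| none (1/1/1) | 62.7% | 61.9% | −0.8 | 5.1% | 5.2% |
| moderate (1.3/1.5/1.5) | 61.7% | 61.9% | +0.2 | 4.5% | 4.9% |
| strong (1.6/2/2) | 58.6% | 60.8% | +2.2 | 3.4% | 4.4% |
| very strong (2/3/3) | 53.3% | 61.5% | +8.2 | 2.7% | 4.9% |

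The Monte Carlo standard error of one power figure is √(0.6 × 0.4 / 3000) = 0.9 points. A second simulation of the same four-stratum comparison gave 62.9 vs 61.9%, 61.0 vs 61.3%, 59.9 vs 62.6% and 50.6 vs 59.4%. Those changes are −1.0, +0.3, +2.7 and +8.8 points. Null rejection in its last case was 3.7 vs 5.1%.

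**Six strata.** With the marginal effect set at the design values of 75% and 50%, about 42 PFS events and 4,000 trials per row, power went from 80.8 to 79.1%, 80.1 to 79.5%, 80.2 to 80.4% and 80.8 to 84.7% from none to very strong. The cost without prognostic effects is a little larger than with four strata (−1.7 points), and gain appears only at the extreme.

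**Hazard ratio.** With a true within-stratum ratio of 0.60 and six strata, the median Cox estimate, unstratified then stratified, was 0.595 and 0.595 (none), 0.600 and 0.592 (moderate), 0.613 and 0.595 (strong), 0.637 and 0.595 (very strong). The shift toward 1 is therefore 0.00, 0.01, 0.02 and 0.04.

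**Primary endpoint.** With moderate factors, adjusting the 18-month difference by pseudo-value regression lowered the mean standard error from 0.1025 to 0.1012, or 0.0013 / 0.1025 = 1.3%. The direct alternative is a stratum-weighted difference of Kaplan-Meier rates with Greenwood variance. Over four strata (4,000 null trials per setting; none, moderate and strong factors) it rejected 6.2%, 6.7% and 6.4%, against 5.5%, 5.3% and 3.8% for the planned test. A separate four-stratum simulation gave 6.0 to 6.6%, and six strata gave about 7%. The Monte Carlo standard error at 5% with 4,000 trials is √(0.05 × 0.95 / 4000) = 0.34 points, so the excess is real.

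**The case against.** The best case for leaving the plan alone has five parts.

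1. The unstratified tests are valid. Null rejection for the log-rank test is at or below nominal, and an unstratified Cox ratio is a legitimate marginal quantity. This stands: the issue is efficiency and choice of target, not error control.
2. The loss is hypothetical. Section 7.4 gives no reason for choosing the factors and no prognostic effects, and with moderate effects nothing changes. This stands too, and it limits the claim to a conditional one.
3. The factors are not wholly absent. Section 10 plans multivariable PFS and ORR models, and Section 10.1.3 looks within the same subgroups. A reader might infer from Section 10.1.2 that every efficacy comparison ignores the factors; that is wider than the text supports. But the models name no covariates, subgroup tests give no pooled stratified comparison, and neither replaces the named tests.
4. An analysis plan could settle it. It could, and Section 10.1.2 does not use the word unstratified. Still, the protocol has already named a test for each endpoint, so a later stratified analysis would depart from the plain reading.
5. Four strata are not the six used at randomisation. True, but they are unions of the randomisation cells, and they avoid cells of two or three patients.

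**Conclusion.** The mismatch is real and modest in size. The named primary and secondary tests between arms do not use the randomisation factors. For the PFS log-rank test at a hazard ratio of 0.50, the cost is about 2 to 3 points of power if the factors are strong and 8 to 9 if very strong, and negligible otherwise. The Cox ratio for PFS moves toward 1 by 0.02 or less up to strong effects and by about 0.04 when they are very strong. All of these sizes rest on assumed prevalences and factor effects.

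Three stronger readings are tempting and not supported. A certain loss of power does not follow, because the documents give no prognostic effects. Nor is the false-positive rate raised; the departure is in the conservative direction. And hazard-ratio shrinkage does not touch the primary endpoint or the ORR chi-square test, since neither estimates a hazard ratio.

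The planned primary test also turns conservative with strong factors (3.8% in the run above), but the simple stratum-weighted replacement errs the other way, so it is no improvement.

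**What to change.** In Section 10.1.2, state that PFS is compared with a stratified log-rank test and a stratified Cox model, that OS is treated the same way, and that ORR is compared with a Cochran-Mantel-Haenszel test. Define four strata from the randomisation record: exon 19 deletion versus any other EGFR mutation, by CNS metastasis yes or no. Keep the unstratified analyses as sensitivity analyses. DoR compares responders only, so the balance argument does not carry over directly and no change is asked for there.

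Leave the primary comparison in Section 10.1.1 as written. If a stratum-weighted Kaplan-Meier difference is wanted, list it as a sensitivity analysis only.

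The cost is wording: no new data are needed, since the randomisation system already holds both factors. If they prove not to be prognostic, the price is about one point of log-rank power. The change should be fixed before any between-arm results are seen.
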